Following baseline, we conducted an ex-post power calculation on our main outcome. Given the prevalence of poor well-being (33.2% - Table 1), and a calculated ICC of 0.026, lower than expected, we determined that we were well powered (> 99%) to detect our original expected 37% relative reduction (an absolute difference of 12% points). Assuming 80% power, the absolute detectible difference is 8% points (a 24% relative reduction). For our other health outcomes, we conducted ex-post power calculations, and determined that we are able to detect a: 7%-point reduction in anxiety, with baseline of 29.7% (ICC: 0.007); 6%-point reduction in depression, with baseline of 20.8% (ICC: 0.01); and 5%-point reduction in emotional distress, with baseline of 17.3% (ICC: 0.005). Given the low prevalence of diarrhea (Table 1) and recent large-scale studies that showed mixed effects of the impact of WASH on diarrhea [48, 49], we considered this a secondary outcome. Given a baseline reported diarrheal prevalence of 9.1% for the index child during the past 7 days (ICC: 0.077), we are powered to see a 6%-point reduction in diarrhea outcomes.

**Table 1 Tab1:** Baseline data

Indicator	Overall		Intervention		Control	
Demographic information	N	%	N	%	N	%
Respondent was female	1589	90.7	793	91.3	796	90.1
Respondent was mother of index child	1589	84.6	793	85.4	796	83.9
Primary caregiver/mother has at least secondary education	1589	12.8	793	11.9	796	13.8
Primary caregiver/mother is married	1587	89.3	792	91.2	795	87.4
Head of household has at least some secondary education	1579	16.7	791	15.2	788	18.2
Demographic information	N	mean (SE)	N	mean (SE)	N	mean (SE)
Respondent’s age	1589	33.5 (0.38)	793	33.7 (0.52)	796	33.3 (0.55)
Head of household age	1589	41.3 (0.46)	793	41.6 (0.54)	796	41.1 (0.73)
Number of household members	1589	5.3 (0.08)	793	5.3 (0.10)	796	5.3 (0.12)
Household latrine coverage	N	%	N	%	N	%
Households with access to at least one household latrine	1589	65.5	793	64.1	796	66.8
Households with access to an improved household latrine ^a^	1553	39.8	775	39.9	778	39.7
Households with access to a fully constructed household latrine	1583	30.7	792	29.6	791	31.9
Household latrine operation and maintenance	N	%	N	%	N	%
Household has added or improved anything on the latrine since its original construction	1028	12.9	504	11.9	524	13.9
Household latrine characteristics	N	%	N	%	N	%
Presence of drop hole cover in the latrine	1033	13.4	505	12.5	528	14.2

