Poor well-being ^c^	1586	33.2 16.0 (7.0)	792	31.1 15.6 (7.1)	794	35.3 16.3 (6.8)

^a^ "Improved" based on the WHO/UNICEF Joint Monitoring Programme (JMP) for Water Supply and Sanitation definition. ^b^ We asked respondents to indicate how much the symptoms bothered them in the previous week with four potential response options (not at all [1] to extremely [4]). The first ten symptoms assess anxiety (i.e., ‘suddenly scared for no reason’, ‘nervousness or shakiness inside’), the next 13 assess depression (i.e., ‘feeling low in energy’, ‘feeling hopeless about the future’), and the 23 collectively assess non-specific emotional distress. For each outcome, the score is the sum of the responses divided by the number of items. Each of these scores was dichotomized, with scores greater than 1.75 indicating a positive status for any of the three outcomes. ^c^ We asked respondents about well-being, and responses ranged from ‘(0) At no time’ to (5) All of the time’. Scores were summed, and range from 0 to 25; the higher the score, the better the well-being. Each of these scores was dichotomized with scores below 13 indicating poor well-being

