Our key health outcome, mental well-being, was shown to be poor, per the WHO-5 scale, amongst approximately one-third of respondents at baseline (Table 1). The baseline prevalence of anxiety, depression, and emotional distress amongst respondents was 29.7, 20.8, and 17.3%, respectively. The distributions of these scores were generally balanced, when comparing the intervention and control arms. Finally, the prevalence of diarrhea during the week (i.e., 7 days) preceding the survey was 9% among index children, and was also generally balanced across study arms (Table 1).

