### Analytical methods

The primary method of analysis for all primary and secondary outcomes will follow an “intention-to-treat” analysis, which compares the intervention arm to the control arm, without regard to intervention fidelity or compliance. For binary outcomes, such as our targeted WASH behaviors, we will preferentially use log-linear binomial regression models. For continuous outcomes, such as the mental well-being scale scores, we will use linear regression models. All models will include an intervention variable as a fixed effect, and account for the stratified design through the inclusion of the *woreda* indicator variable [52], and incorporate generalized estimating equations with robust standard errors to account for the clustering of observations within *kebeles*.

The majority of our primary and secondary outcomes (shown in Additional file 5: Table S3) are binary variables, and for these we will preferentially use log-linear binomial models; however, log-linear binomial models are known to have difficulty converging, and so we may instead use modified Poisson regression if we encounter problems with convergence [53]. There is often interest in showing an absolute measure along with a relative measure (e.g., a prevalence ratio), so we will also present prevalence differences. We will use the same models as described above (e.g., log-linear binomial models), but use post-estimation commands to estimate the average marginal effects.

Given no imbalances were detected between study arms at baseline for any of the primary variables of interest (Table 1), we will not need to perform supplementary analyses, as outlined in our pre-analysis plan, to control for the baseline levels of these imbalanced variables in more fully adjusted models. For many of our outcomes, there is interest in determining the impact of the intervention across various sub-groups, such as sex, follow-up round (once multiple rounds of collection are completed), exposure to previous triggering, and modifiers such as water and sanitation insecurity. For select key outcomes, we will use interaction terms and/or stratification, and we will present the impact of the intervention at each level of the sub-group variable (e.g., separately for boys and girls).

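### Table 1's WHO-5 mean and poor well-being share point in opposite directions by arm; a table error is very likely, so it is unclear which arm started worse

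*Protocol article*

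**What the plan says.** All references are to the protocol article. Study outcomes and measures names the WHO-5 as one of two instruments for the primary outcome of mental well-being. In Sample size, the paragraph after the original calculation opens "Following baseline, we conducted an ex-post power calculation on our main outcome" and continues "Given the prevalence of poor well-being (33.2% - Table 1), and a calculated ICC of 0.026, lower than expected". So the main outcome there is the share with poor WHO-5 well-being, although the original sample size was based on the Hopkins Symptom Checklist.

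Footnote c of Table 1 gives the direction of the scale, "Scores were summed, and range from 0 to 25; the higher the score, the better the well-being", and the cut-off, "Each of these scores was dichotomized with scores below 13 indicating poor well-being". The WHO-5 row reads:

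| | N | % poor | Mean (SD) |
|---|---|---|---|
| Overall | 1586 | 33.2 | 16.0 (7.0) |
| Intervention | 792 | 31.1 | 15.6 (7.1) |
| Control | 794 | 35.3 | 16.3 (6.8) |

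Balance of treatment arms at baseline says of the anxiety, depression and distress prevalences and the scores behind them: "The distributions of these scores were generally balanced, when comparing the intervention and control arms". Analytical methods then relies on the table, "Given no imbalances were detected between study arms at baseline for any of the primary variables of interest (Table 1"), to set aside the supplementary baseline-adjusted models foreseen in the pre-analysis plan. None of these sections remarks that the two WHO-5 statistics disagree on which arm is better off.

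**The concern.** A lower mean on a scale where higher is better should go with more respondents below a fixed cut-off, and a larger SD pushes the same way when the cut-off lies below the mean. The intervention arm has the lower mean and the larger SD, yet the smaller share below 13. The two gaps are also of almost the matching size with the wrong relative sign, which is what an exchange of one statistic between columns would produce.

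At stake is the baseline position of the arms on a named primary measure. Analytical methods plans linear regression for the well-being scale scores and log-binomial regression for binary outcomes, so both forms of the measure matter. A reader of the endline result will want to know which arm started worse, and the row gives two opposite answers.

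**Working it through.** **Inputs.** Ns, percentages, means and SDs from the WHO-5 row of Table 1; scale and cut-off from footnote c; ICC 0.026 from Sample size; 50 clusters.

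**1. Reproduce the overall row.** Share: (792 × 31.1 + 794 × 35.3)/1586 = 33.2%. Mean: (792 × 15.6 + 794 × 16.3)/1586 = 15.95, printed as 16.0. The row reproduces. Because the arms are almost equal in size, it would reproduce just as well after an exchange (33.2%, 15.95), so the overall column cannot show whether one took place.

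**2. Share below 13 implied by each arm's mean and SD.** Normal approximation with the cut at 12.5:
- Intervention: Φ((12.5 − 15.6)/7.1) = 33.1%.
- Control: Φ((12.5 − 16.3)/6.8) = 28.8%.

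Two distributions confined to 0–25 agree on the direction:

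| Model | Intervention | Control | Difference |
|---|---|---|---|
| Normal | 33.1% | 28.8% | +4.3 |
| Maximum entropy on 0–25 | 32.2% | 28.1% | +4.1 |
| Beta-binomial on 0–25 | 33.3% | 29.2% | +4.1 |
| Printed | 31.1% | 35.3% | −4.2 |

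If the mean (SD) pairs are exchanged, the normal-implied difference becomes −4.3 against −4.2 printed.

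**3. Is the printed row possible at all?** A linear program over all distributions on 0–25 with the stated mean and SD gives a feasible share below 13 of 8–67% (intervention) and 5–64% (control). Both printed cells lie inside, so the row is not arithmetically impossible.

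**4. How implausible is it?** Average cluster size 1586/50 = 31.72; design effect 1 + 30.72 × 0.026 = 1.80.
- Mean difference: SE = √1.80 × √(7.1²/792 + 6.8²/794) = 0.47; z₁ = −0.7/0.47 = −1.5.
- Share difference: SE = √1.80 × √(0.311 × 0.689/792 + 0.353 × 0.647/794) = 3.2 points; z₂ = −4.2/3.2 = −1.3.

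Each gap alone is ordinary. But the score and poor status must be negatively correlated. Given the overall row, the correlation is at least 0.61 in size by linear program, and about 0.77 if the score is roughly normal. If the arms share one distribution, the joint statistic is (z₁ + z₂)/√(2(1 − r)):
- r = 0.61: −2.82/√0.78 = −3.2 (p about 0.0014).
- r = 0.77: −2.82/√0.46 = −4.2 (p about 0.00003).

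Taking the mean gap as 0.6, to allow for rounding of both means, gives about −2.9 with r = 0.61. Replacing 0.026 by the protocol's planning ICC of 0.05 for both statistics (design effect 2.54) gives −2.7 to −3.5.

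**5. Which statistic is likelier to have moved?** 246/792 = 31.1% and 280/794 = 35.3%, so the percentages fit their printed Ns. Had the percentages been exchanged, 35.3% would need a count out of 792, and none gives it: 279 gives 35.2% and 280 gives 35.4%. The Ns cannot have been exchanged either, since 794 exceeds the 793 households enrolled in the intervention arm. This points to the mean (SD) pair. It assumes unweighted percentages, and three other percentage cells in Table 1 fail the same check, so it is an indication only.

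**6. Other slips in the table.** Washing-station coverage overall (78.9%) lies above both arms (77.1% and 78.8%). The 7-day diarrhea N for control is 797 against 796 enrolled. The latrine-sharing Ns add to 506 + 530 = 1036, not 1037. These make a transcription error in the WHO-5 row credible.

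**The case against.** The strongest reply is that nothing fails arithmetically. The overall row pools, both cells are feasible, and the intervention cell taken alone is unremarkable (32.2% by maximum entropy against 31.1% printed). Only the control cell looks odd, and poor scores bunched just below the cut-off could produce it. The normal model is also rough here: with mean 16 and SD 7 it puts about 9% of respondents above the scale maximum. All of this stands, and it is why the row is called implausible rather than impossible. It does not remove the joint result in step 4, whose lower figure uses a correlation bound that needs no distributional shape.

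A reader might go further and infer three things that the document does not support.
- That the percentages were the cells exchanged. The integer check leans the other way, and a single-cell error is also possible.
- That the balance conclusion rests on the error. An exchange changes the sign of one gap but not its size (z about 1.3 and 1.5 in either case), so the statement of no imbalance stands or falls as before.
- That arm codes are wrong in the analysis file and an endline effect will have the wrong sign. A slip confined to one table row explains the pattern equally well, and nothing in the article shows miscoded data.

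It can also be said that adding a covariate is a preference, since the planned models contain only treatment and woreda. It is true that the discrepancy alone does not require it. But the stated reason for dropping baseline adjustment is Table 1, and that table includes this row.

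**Conclusion.** The point holds as a reporting inconsistency in a primary measure. The WHO-5 mean and the poor well-being share disagree on which arm was better off at baseline. Under a common baseline distribution the disagreement has a joint z of about −3 to −4. This rests on two assumptions: that the arms were drawn from one population, and that the ICC of 0.026, reported with the prevalence of poor well-being, also applies to the score. A table error is therefore very likely but not proven. An exchange of the mean (SD) pair is the leading explanation.

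The consequence is limited. The pooled 33.2%, the power inputs and the absolute gaps of 4.2 percentage points and 0.7 score points do not change. What cannot be read from the article is the direction of the baseline difference on the outcome that Sample size calls the main one.

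**What to change.** 1. Recompute the WHO-5 mean (SD) and the share below 13 by arm from the raw items, using one arm variable for both.
2. Confirm that the arm coding in the analysis file is right.
3. Correct the WHO-5 row of Table 1, or confirm it and explain the distribution that produces it.
4. State the direction of the baseline WHO-5 difference in Balance of treatment arms at baseline and in Analytical methods.
5. Include the verified baseline WHO-5 value as a covariate in the WHO-5 models, instead of dropping baseline adjustment because Table 1 showed no imbalance.

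The cost is one data check, one table row, a sentence or two of text and one covariate that has already been collected. No new data are needed, and the sample size is unaffected.

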### Eligibility criteria

Rural and peri-urban *kebeles* within Bahir Dar Zuria, Fogera, and Farta *woredas* that are accessible throughout the course of the year were eligible for inclusion in the *Andilaye* Trial. This decision was made in partnership with relevant *Woreda* Health Offices and One WASH National Program representatives, as officials from these areas were meant to facilitate and supervise the implementation of the *Andilaye* intervention. Officials from relevant *Woreda* Health Offices helped study staff identify *kebeles* that met these eligibility criteria. While sanitation coverage and utilization were originally incorporated as inclusion criteria, the veracity of existing data were not verifiable in many *kebeles* in which initial visits were made. For example, only one latrine was observed in a community in which sanitation coverage was reportedly over 80%, and the community reported this being the case for as long as people could recall. Due to uncertainty regarding sanitation coverage and utilization data, and the challenge of behavioral slippage even in *kebeles* previously declared as open defecation free (ODF), those criteria were dropped from inclusion requirements prior to baseline data collection. As such, any *kebele* meeting the previously stated eligibility criteria was eligible, regardless of sanitation coverage and utilization or previous CLTSH triggering or ODF verification status.

We employed a structured sampling strategy to randomly select eligible *kebeles* within the sampling frame. The primary sampling unit for this study was the *kebele*. The secondary sampling unit for this study was the household; specifically, any household residing in a targeted, sentinel village (*gott*) within a randomly selected study *kebele*. While we randomly selected eligible study clusters (i.e., *kebeles*), we purposively selected *gott(s)*, from which we randomly selected study households. We utilized a ‘fried egg’ [50] approach to purposively select one to two *gotts* that were either situated in or near the center of the *kebele* (if there were centric *gotts*) or were not adjacent to any other study *kebele* (in the event there are no centric *gotts*). This approach minimized spill-over of intervention effects and other externalities associated with the research between intervention and control clusters, especially those adjacent to each other. The number of targeted *gotts* depended only on the number of eligible households identified in *gott* census books. Study household inclusion criteria for the *Andilaye* Trial included any household randomly selected from the *gott* census book residing in the target *gott*(s) that: (1) had at least one child aged 1–9 years at baseline (i.e., the study’s index children) and consented to allowing study staff to observe the children, specifically their faces and hands, and (2) provided consent to participate in the study, with at least one adult household member consenting to serve as the primary survey respondent.

### Recruitment

From the *kebele* sampling frame, we employed a random number generator to identify 50 eligible *kebeles* clusters from across the three *woredas* targeted for our study. Given each of the three *woredas* vary with regard to their hydrogeological conditions and the size and number of *kebeles*, we used a stratified selection approach (at the *woreda* level). Of the 50 clusters, 22 were selected from Farta, 12 from Fogera, and 16 from Bahir Dar Zuria. Proportionally, these selected *kebeles* represented 51 (22/43), 38 (12/32), and 50 (16/32) percent of all *kebeles* in Farta, Fogera, and Bahir Dar Zuria, respectively. An even number of clusters were selected from each *woreda* to ensure an equivalent sample size between the intervention and control clusters selected from each *woreda*. Fogera had a slightly lower proportion of selected *kebeles* due to accessibility concerns given the frequency of floods in the low-land, marshy areas close to Lake Tana (Fig. 1). Our baseline results indicated that 78% (39 of 50) of *kebele* clusters randomly selected for inclusion in the *Andilaye* Trial have been triggered with CLTSH, and certified as ODF according to *Woreda* Health Office records. Another 14% (7 of 50) of study clusters have been triggered with CLTSH but have not yet been certified ODF, and the remaining 8% (4 of 50) have not been triggered with CLTSH, as of the commencement of this study, though they are slated for triggering.

Recruitment took place within the home compounds during baseline data collection. Enumerators contacted adult members of the household; they explained the purpose of the visit, the purpose of the study, and asked the respondent if s/he would be willing to consent to participate in the study using a structured consent form (Additional file 4). Enumerators assessed household level eligibility by asking potential survey respondents a series of questions that lead to a determination of eligibility, and enrolled eligible and consenting households into the trial. During the consent process, enumerators informed respondents that they had the right to choose not to participate in the study, the right to refuse to answer any question, and the right to stop the survey for any reason at any point in time. Enumerators targeted primary survey respondents, based on the following order of priority: (1) the primary female caregiver of the index child, (2) any female household member who serves as a caregiver, (3) any male household member who serves as a caregiver, and (4) any household member over 18 year of age. If households were absent after three visits, no eligible adult respondent was available or refused to consent, or upon further conversation with the household, it became apparent that it was not eligible (e.g., no child aged 1–9 years), the enumerator recorded the information and notified the field supervisor prior to replacing that household with the next randomly selected household on the study roster. Of 1691 surveys initiated during baseline, 1589 (94%) households met all inclusion criteria and were enrolled into the study – 89 households more than the targeted sample size. Targeted households that did not meet inclusion criteria were excluded for the following reasons: 81 households did not have a household member between 1 and 9 years of age, 17 households had no eligible respondent available, three surveys were initiated but not fully completed, and one household did not consent to participate.

### Random allocation

Following baseline data collection, we used a stratified random design to assign study *kebeles* to either the *Andilaye* intervention or control arm (CLTSH). Within each stratum (*woreda*), researchers from Emory University in Atlanta, USA used a computer-based random number generator to generate a random number between zero and one for each *kebele* cluster, and then placed the clusters in ascending order by their randomly generated numbers. We then partitioned the communities within each *woreda* into two equal sizes, assigning the first half of *kebeles* to the intervention arm and the second half to the control arm. We used replacement re-randomization [51] to secure balance across three key variables (latrine coverage, washing station with soap coverage, and head of household education), as indicated by our baseline survey. CRTs, particularly trials with a small number of clusters, often have individual-level imbalances between study arms. Therefore, we established a priori that the intervention and control mean values for these three variables should be within two standard deviations of the overall mean for these variables. The randomization process described above was repeated (twice) until these variables were balanced according to that *a prior* criterion. Results from our equivalence analyses indicated balance in the number of previously triggered and ODF certified *kebeles*, between study arms, with 20 triggered and ODF *kebeles* in the intervention arm (80%, 20 of 25 study clusters) and 19 in the control arm (76%, 19 of 25 study clusters). Figure 3 provides further details in a flow diagram.

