### Sample size

We powered this study on mental well-being outcomes, as measure by the HSCL [41], which reflected the most restrictive primary outcomes in terms of required sample size. Various studies from Ethiopia and East Africa suggest that approximately 20–35% of rural women experience elevated symptoms of common mental disorders such as anxiety and depression [44, 45]. Drawing on two studies that have used the HSCL in East Africa [41], we estimated that average scores generated by this tool would be around 1.5 (SD 0.5). Using unpublished data from a large on-going study of young people in Ethiopia [46], we estimated the intra-cluster correlation (ICC) for a measure of mental health was approximately 0.05, although we suspected this may be low given the sample consists of young people, and the measure captures more severe mental health symptoms. Unpublished data from rural households in South Omo, Ethiopia are approximately 33% higher on a common mental health scale; suggesting that water insecurity is linked to mental health, and the effect is appreciable [47]. There are limited data on the impact of changes in WASH on mental well-being, so we used a similar difference to estimate our impact. Our sample size determination (Additional file 3: Table S2) indicated that we should recruit and enroll a total of 25 households from each of 50 study clusters (25 clusters per study arm). We increased our final sample size to accommodate for 20% of households being lost to follow-up. Our target sample, therefore, included 30 households in each *kebele* study cluster, or 1500 households in total (i.e., 750 per study arm).

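### The re-randomization rule as written cannot reject any equal split, which contradicts the reported repeats and leaves the real constraint on the allocation unknown

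*Protocol article*

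**What the plan says.** Under Random allocation, kebeles were ordered by random number within each woreda and divided "into two equal sizes, assigning the first half of" kebeles to the intervention arm and the rest to control. The Recruitment section gives strata of 22, 12 and 16 kebeles, so the split is 11/11, 6/6 and 8/8, or 25 against 25.

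The allocation was then checked for balance: "We used replacement re-randomization [51] to secure balance across three key variables (latrine coverage, washing station with soap coverage, and head of household education"). The acceptance rule reads: "we established a priori that the intervention and control mean values for these three variables should be within two standard deviations of the overall mean". The section does not say whether the SD is that of households, of kebele values or of a mean. It goes on: "The randomization process described above was repeated (twice) until these variables were balanced" by that rule.

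Under Analytical methods: "All models will include an intervention variable as a fixed effect, and account for the stratified design through the inclusion of the" woreda indicator, with generalized estimating equations and robust standard errors for clustering by kebele. None of the three balance variables is named as a covariate. The section adds that the further baseline-adjusted models foreseen in a pre-analysis plan are not needed, because no imbalance was found at baseline.

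**The concern.** Re-randomization works by discarding allocations that fail a stated rule. Its effect on balance, and on the inference that follows, depends on how often the rule discards a draw. Here the stated rule seems too wide to discard anything, yet the text reports that draws were repeated. Both statements cannot be true of the same rule.

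Two things are at stake. First, a reader cannot reconstruct the set of allocations from which this one was drawn, and so cannot judge the claim that balance was secured. Second, the models carry the stratification factor but not the re-randomization variables. If the rule actually used was tight, an analysis that ignores it gives standard errors that tend to be too large for outcomes related to latrine coverage, washing stations with soap or household education. The first two plausibly bear on the primary sanitation and hygiene outcomes. If the rule never discarded a draw, leaving the variables out gives up possible precision.

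**Working it through.** **Inputs.** 50 kebeles, 25 per arm, in strata of 22, 12 and 16 (Recruitment; Random allocation). 793 intervention and 796 control households (Table 1). Latrine access 65.5% overall, 64.1% v 66.8% by arm. Head of household with some secondary education 16.7% overall, 15.2% v 18.2% by arm. Washing stations with soap do not appear as such in Table 1. Average households per kebele: 1589/50 = 31.8.

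**1. Largest possible deviation.** For arms of n1 and n2 units, the between-arm variance cannot exceed the total variance. Hence |mean of arm 1 − overall mean| ≤ SD × √(n2/n1).
- Kebele level, 25 v 25: √(25/25) = 1.00 SD (0.99 with the n−1 SD).
- Household level, 793 v 796: √(796/793) = 1.002 SD.

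The permitted distance is 2 SD, about twice the largest distance that can occur. The probability of rejection is exactly 0 for any equal split and any variable. In 100,000 simulated stratified draws on three independent normal kebele-level variables, the largest deviation was 0.63 SD and no draw was rejected.

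**2. The rule in percentage points (household SD).**
- Latrine: SD = √(0.655 × 0.345) = 0.475; accepted range 65.5 ± 95.1, or about −30% to 161%.
- Education: SD = √(0.167 × 0.833) = 0.373; accepted range 16.7 ± 74.6, or about −58% to 91%.

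**3. The reported repeats.** Under the written rule the expected number of repeats is 0. Whether the phrase means two further draws or two draws in all, at least one draw was set aside, so the reported process is not reproduced.

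**4. What if a standard error was meant?** Write S for the SD of kebele values. When 25 of 50 kebeles are drawn, the deviation of the arm mean has randomization SD S × √((1/25) × (1 − 25/50)) = S/√50 = 0.141 S (simulated: 0.142 S). For a limit L, one variable is rejected with probability p = 2 × [1 − Φ(L/0.141 S)], and three independent variables with probability 1 − (1 − p)³.

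For the household-level reading, L = 2/√795 = 0.071 household SD. One kebele SD is √(ICC + (1 − ICC)/31.8) household SD. The intra-cluster correlations (ICCs) of these variables are not given; 0.05 to 0.30 is my assumption.

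| Reading of the limit | L in units of S | p | Reject, three variables | Simulated |
|---|---|---|---|---|
| 2S/√25 | 0.400 | 0.005 | 1.4% | 1.1% |
| 2S/√50 | 0.283 | 0.046 | 13.0% | 12.7% |
| 2 naive household SEs of an arm mean, ICC 0.05 | 0.251 | 0.076 | 21.1% | 21.3% |
| Same, ICC 0.10 | 0.198 | 0.161 | 41.0% | 41.9% |
| Same, ICC 0.20 | 0.149 | 0.290 | 64.3% | 65.3% |
| Same, ICC 0.30 | 0.125 | 0.377 | 75.8% | 76.6% |

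Two rejections in a row have probability of about 1.7% on the second row (0.130²), but about 57% on the last (0.758²). Some readings make the reported repeats unremarkable; others make them very unlikely.

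**5. Observed balance.** The largest arm deviations in Table 1 are 1.4 points for latrine (1.4/47.5 = 0.03 household SD) and 1.5 points for education (1.5/37.3 = 0.04 household SD).

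**The case against.** The best defence is that the sentence is loosely worded and that a standard error, or some other sampling SD, was coded. The report of repeats supports this, since a rule that could reject was evidently in use. The section motivates the rule by individual-level imbalance, which makes a household-level reading plausible, and on that reading one or two repeats are ordinary. This stands. It means that the inertness belongs to the written rule, not necessarily to what was done. It does not rescue the sentence, because the readings differ so much in how tightly they constrain the allocation.

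A reader might infer that no balance was secured, or that draws were discarded at will and the randomization is suspect. The document supports neither. It describes computer-generated numbers, equal splits within strata, variables and a criterion fixed in advance, and a rule that treats both arms alike. Redrawing under such a rule does not bias the comparison.

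Nor does the omission of the three variables invalidate the analysis. If the rule bound, inference is conservative; if it did not, some precision may be lost. The text calls the variables key, not prognostic, and shows no link to the mental well-being scores. The Table 1 gaps are small.

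Two further points stand in part. The flow diagram, the cited method and the pre-analysis plan are not in view and may hold the real rule, but the published sentence is still wrong. And endline ran from March to May 2019 while the article appeared on 21 June 2019, so adding covariates to the primary model at that date could be a change made after outcomes were known. The fix allows for this.

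**Conclusion.** The point holds for the criterion as written. Its rejection probability is exactly 0, by an algebraic bound that needs no assumption beyond equal arms. It therefore cannot secure balance, and it is incompatible with the reported repeats. A different threshold was probably used, and the text does not reveal which. Under the standard-error readings tried, the chance of rejecting a draw runs from about 1% to about 76%; those figures rest on three independent, roughly normal kebele-level variables and, for the household-level reading, on assumed ICCs of 0.05 to 0.30.

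No imbalance or bias is shown. The consequence is an allocation rule that cannot be reproduced, together with an analysis that is either conservative for related outcomes or less precise than it could be. This should be corrected, but it does not undermine the trial's validity.

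**What to change.** 1. Replace the criterion sentence with the rule actually coded: the metric (household SD, kebele SD or a standard error), the threshold, the number of draws made and rejected and why, and the acceptance probability obtained by re-running the allocation code.
2. Include the baseline values of the three re-randomization variables alongside woreda in the models. Make this the main adjusted analysis if outcome data have not been seen; otherwise report it as a declared sensitivity analysis.
3. If the acceptance probability is materially below 1, confirm the primary p-values with a permutation test restricted to allocations that meet the same rule.

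The cost is one corrected sentence, three covariates already collected, possibly one permutation run, and a documented change to the analysis plan. No new data are needed.
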